## 2. Materials and Methods

### 2.1. Study Design and Setting

This project will be a prospective, randomized, double-blind, placebo-controlled clinical trial designed to evaluate the efficacy and safety of NBO therapy in patients diagnosed with CRC undergoing chemotherapy. The study will be conducted in a tertiary hospital setting, ensuring access to standardized treatment protocols and comprehensive patient monitoring. Only NBO operators responsible for therapy administration will be unblinded in order to ensure proper intervention delivery.

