### 2.5. Randomization and Blinding

Participants will be randomized in a 1:1 ratio to the active NBO (study) or placebo NBO (control) group using a stratified randomization method. Stratification factors include CRC stage (II vs. III vs. IV) and baseline hemoglobin levels (<12 g/dL vs. ≥12 g/dL), as these variables can significantly influence treatment outcomes and the incidence of anemia. A computer-generated allocation sequence will be used within each stratum to ensure an even distribution of these characteristics across the two study arms. Only the NBO operators (who are not involved in data collection or analysis) will have access to the allocation list to administer the assigned intervention. All other study personnel and participants will remain blinded to group assignments.

Patients and clinical staff (excluding NBO operators who administer the therapy) will be blinded to the treatment allocations. Placebo NBO sessions mimic active NBO conditions without therapeutic oxygen adjustments. Both patients and clinical staff involved in patient care and data collection will be blinded to the treatment allocations. NBO operators who administer the therapy will not be blinded in order to ensure the correct delivery of the intervention. They will be trained to maintain confidentiality and avoid any disclosures that could compromise blinding. Both active NBO and placebo NBO sessions will be conducted in chambers that are identical in appearance and setup. This includes similar equipment, procedures, and environmental conditions in order to prevent patients and blinded staff from discerning group assignments.

Unblinding will occur after the database is locked and completion of statistical analysis. Immediate unblinding is permissible in medical emergencies where treatment knowledge is essential for patient care. Unblinding may occur immediately if a serious adverse event or medical emergency arises where knowledge of the treatment allocation is essential for the patient’s safe and effective management. The decision to unblind in an emergency will be made by the principal investigator or a designated medical officer.

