For the CRC groups (Groups 1 and 2), it was determined that 127 patients per group are required. This accounts for a potential 30% dropout rate, ensuring that the final sample maintains the desired power and accounting for the challenges associated with patient retention over the study period. The sample size calculations were performed using G*Power software (version 3.1.9.7 or the latest version). The parameters used in the calculation included the expected effect size (d), calculated based on the anticipated difference and standard deviation from pilot studies or the existing literature. An allocation ratio (N2/N1) of 1 was used, indicating equal allocation between the active NBO and placebo groups. The test family selected was *t*-tests for means between two independent groups, focusing on the difference between two independent means.

Assumptions made during the calculation included a confidence level of 95% and the use of a two-tailed test, considering the possibility of the effect in both directions. It was also assumed that the variability in outcome measures would be similar across groups, which is important for the validity of the statistical tests used.

The rationale for this sample size is to ensure that the study is sufficiently powered to detect clinically meaningful differences between the active NBO and placebo groups in the primary outcome measures. By accounting for a 30% dropout rate, the study design acknowledges the realities of clinical research involving patients undergoing chemotherapy, who may experience side effects or other factors leading to withdrawal from the study.

An interim analysis will be conducted after 50% of participants have completed the study. The research team will assess data on safety and efficacy trends during this analysis. Based on interim findings, sample size adjustments may be considered, adhering to statistical guidelines to control for Type I error inflation and ensuring the integrity of the study.

Statistical analyses will be performed using software such as SPSS (version 26 or later) and R (version 4.0 or later) with appropriate packages. Supplemental tools like SAS 9.4 M8 or Stata 19 may be used if needed. Data management will involve entering data into a secure database with validation checks to ensure accuracy. Data cleaning procedures will be implemented prior to analysis to address any inconsistencies or errors.

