### 2.13. Safety Evaluation

The safety of participants will be continuously monitored throughout the study to ensure early detection and appropriate management of adverse events (AEs) and serious adverse events (SAEs). Investigators will conduct regular clinical assessments, laboratory evaluations, and vital sign monitoring at each study visit. All AEs and SAEs will be classified according to their severity (mild, moderate, or severe) and their relationship to the intervention (related, possibly related, or unrelated).

The study may be terminated or modified in response to safety concerns, including the emergence of new, unknown adverse reactions that undermine the previously justified benefits of study participation. If new adverse reactions are identified during the study that pose a significant risk to participants, the risk–benefit assessment will be re-evaluated, and continuation of the trial will be reconsidered. Unexpected severe side effects related to NBO therapy or chemotherapy that cannot be managed with standard medical interventions may necessitate protocol modifications or early termination.

In cases where adverse reactions to the therapeutic management reach a level of severity that prevents the trial from continuing safely, the study may be discontinued. Additionally, if the sponsor determines that the study cannot proceed due to a serious violation of Good Clinical Practice (GCP) by an investigator, appropriate actions will be taken, including reporting to regulatory authorities and the ethics committee.

All SAEs will be reported to the ethics committee and regulatory authorities within the required timeframe. An independent Data Safety Monitoring Board (DSMB) will periodically review all safety data to provide recommendations on study continuation, modifications, or termination. Any safety-related findings will be documented in the final study report and considered in future research planning.

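### Section 2.10 gives the research team an interim look at efficacy trends, which it cannot take by arm without breaking the blind set in sections 2.1 and 2.5

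*Protocol article*

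**What the plan says.** Four places in the protocol article bear on this point.

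- **Section 2.10 (Statistical Analysis), the interim.** "An interim analysis will be conducted after 50% of participants have completed the study". On who looks, and at what: "The research team will assess data on safety and efficacy trends during this analysis". On what may follow: "Based on interim findings, sample size adjustments may be considered, adhering to statistical guidelines to control for Type I error inflation".
- **Section 2.1 (Study Design and Setting).** "Only NBO operators responsible for therapy administration will be unblinded in order to ensure proper intervention delivery".
- **Section 2.5 (Randomization and Blinding).** The allocation list is open to the operators alone, and they take no part in data collection or analysis. For the rest: "All other study personnel and participants will remain blinded to group assignments". On timing: "Unblinding will occur after the database is locked and completion of statistical analysis". The one exception is a serious adverse event or medical emergency in which the patient's care depends on knowing the treatment. No exception is made for an interim analysis.
- **Section 2.13 (Safety Evaluation).** "An independent Data Safety Monitoring Board (DSMB) will periodically review all safety data". The board advises on whether the trial continues, changes or stops. No role in reviewing efficacy or sample size is stated.

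**The concern.** In a two-arm placebo-controlled trial, a trend in efficacy ordinarily means a difference between the arms. The sentence on sample size supports that reading: a review of pooled variance and dropout would hardly raise the Type I error concern that the article mentions. A comparison by arm needs allocation data, and sections 2.1 and 2.5 withhold those data from the people given the task.

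The blind is at stake. If the research team sees the emerging effect, later decisions on recruitment, retention and withdrawal can be coloured by it. Section 2.11 leaves the principal investigator discretion over withdrawal. Double-blinding is the trial's central design claim, so the article should not leave open whether it holds from half-way onwards.

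**Working it through.** **Step 1. Who may do the interim by arm?** Setting the sections side by side:

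| Party | Assigned to the interim? | May see allocation? |
|---|---|---|
| NBO operators | No; kept out of data collection and analysis (2.5) | Yes (2.1, 2.5) |
| Research team | Yes (2.10) | No, until after lock and analysis (2.5) |
| DSMB | Safety review only is stated (2.13) | Not stated |

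No row has yes in both columns. Masked arm labels do not resolve this. Someone outside the operators would still have to split the data by arm, and the team would still see the size of the difference.

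**Step 2. How much of the trial would follow the look?** The article gives no accrual curve, so this is a range under stated assumptions.

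Inputs:
- Planned total: 2 × 127 = 254 (sections 2.6.2 and 2.10).
- Dropout: 30% (section 2.10).
- First enrolment: March 2026; screening finalised in 2028; recruitment completed by 2030 (section 3). Assumption: uniform accrual from March 2026 to the end of 2028 (34 months) or to the end of 2029 (46 months).
- Time from randomisation to V5: the session period plus 6 months. Section 2.6 puts the ten sessions in 5 weeks; section 2.7 and Table 1 spread them over 10 weeks. Both are used here, and the sections need reconciling. 35/30.4 + 6 = 7.2 months; 70/30.4 + 6 = 8.3 months.

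Formula: enrolled at the interim = R + (254 / accrual months) × months to V5, where R is the number randomised early enough to have reached V5.

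Accrual rate: 254/34 = 7.47 per month; 254/46 = 5.52 per month.

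Reading A, in which half of those planned have passed V5 with dropouts counted: R = 127, or 127 × 0.7 = 89 actual completers.
- Low: 127 + 5.52 × 7.2 = 167, or 66% enrolled, leaving 34%.
- High: 127 + 7.47 × 8.3 = 189, or 74% enrolled, leaving 26%.

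Reading B, in which 127 patients have actually completed: R = 127/0.7 = 181.
- Low: 181 + 5.52 × 7.2 = 221, or 87% enrolled, leaving 13%.
- High: 181 + 7.47 × 8.3 = 243, or 96% enrolled, leaving 4%.

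Across both readings, 4% to 34% are still to be enrolled. A further 5.52 × 7.2 = 40 to 7.47 × 8.3 = 62 patients have been randomised but have not reached V5 (before dropout).

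**Step 3. Type I error for the action the article names.** The only stated consequence is a change of sample size. Suppose the size could only be increased on comparative data and the final test were left uncorrected, contrary to what section 2.10 promises. The worst-case one-sided error would then rise from 0.025 to 0.029 (total up to 1.5 times planned) or 0.031 (up to 2 times). Proper control would remove that excess.

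The 127 per group is not in question here. The article gives no numeric effect size or standard deviation, so it cannot be reproduced uniquely, and nothing above tests it.

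**The case against.** The strongest reply is that section 2.10 never says the look is by arm, unblinded or tested, and never defines the research team. A pooled review would be consistent with section 2.5. That is fair: the conflict comes from the natural reading of the words and is not an explicit statement that the team is unblinded. But if a pooled review is meant, the article has to say so, because efficacy trends coupled with a Type I error concern point the other way. Either reading calls for a correction.

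A reader might also infer several stronger things that the article does not support.

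- **That Type I error is ignored, or rises to 8.3%.** Testing at two-sided 0.05 both half-way and at the end would give 0.083. That needs an efficacy claim at the interim. Section 2.10 names only a sample size change, and the termination grounds in section 2.12 are safety, ethics and operations. Error control is promised in general terms, and the method may be left to an SAP.
- **That a third of patients are always still to be enrolled.** That is the top of the range. It falls to 4% to 13% if 127 actual completers are needed at the stated 30% dropout.
- **That outcome ratings would be biased.** The primary outcomes are mainly laboratory measures, and the secondary ones are self-reports from patients who stay blinded. No investigator-rated efficacy scale is described.
- **That there is no independent board, or that it is barred from efficacy.** A DSMB exists. Section 2.13 gives it no efficacy role but does not exclude one.

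**Conclusion.** The concern holds as a conflict over who sees comparative data. Read naturally, section 2.10 gives the research team a look that sections 2.1 and 2.5 do not allow it to take, and section 2.13 does not assign that look to anyone else. The exposure is 4% to 34% of patients still to be enrolled and about 40 to 62 more not yet at V5. These figures rest on uniform accrual over 34 to 46 months, 7.2 to 8.3 months to V5, and the two readings of completion. The conflict itself depends on none of them. No inflation of Type I error is shown, and the likely harm runs through trial conduct rather than outcome assessment.

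**What to change.** Reconcile sections 2.1, 2.5, 2.10 and 2.13 by stating one of the following:

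- **(a)** The research team's interim review, and any re-estimation of sample size, use blinded pooled data only: pooled standard deviation, dropout and overall safety.
- **(b)** Comparative interim data go only to the existing DSMB, prepared by a statistician outside the research team, and the team receives only a recommendation. Sections 2.1 and 2.5 then need a matching exception for that statistician and the board, and section 2.13 needs the wider remit.

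In either case, add that the interim allows no early efficacy claim, and say whether the 50% counts actual completers or patients who have reached V5 with dropouts included. Re-estimation based on the observed effect need not be banned: under (b) it is legitimate if the promised error control is applied.

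The cost is wording in the protocol and, under (b), in the DSMB's terms, plus a statistician outside the team. The team gives up sight of interim efficacy by arm. The 127 per group does not change. With first enrolment scheduled for March 2026, the text should be corrected before then, or at the latest before the interim.

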Handling of missing data is an important aspect of the analysis plan. An intention-to-treat (ITT) analysis will be conducted, including all randomized patients in the analysis according to their assigned groups. Missing data will be handled using appropriate statistical methods such as multiple imputation or last observation carried forward (LOCF), depending on the nature and extent of the missing data. Additionally, a per-protocol (PP) analysis will be conducted as a secondary analysis, including only patients who completed the study without major protocol deviations, to assess the robustness of the findings.

Adjustment for multiple comparisons will involve the use of Bonferroni correction or other suitable methods when conducting multiple statistical tests. This approach helps control the overall Type I error rate, reducing the likelihood of false-positive findings due to multiple tests. Sensitivity analyses will also be performed to assess the robustness of the results under different assumptions and statistical models, providing additional confidence in the study conclusions.

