### 2.11. Patient Withdrawal

Participants may be withdrawn from the study under specific conditions to ensure safety, data integrity, and adherence to protocol requirements. Voluntary withdrawal allows participants to withdraw consent at any time without penalty or loss of benefits, and they are not required to provide a reason. Medical reasons for withdrawal may arise if the investigator determines that continued participation is not in the patient’s best medical interest due to medical conditions or adverse events that pose a risk. Eligibility non-compliance may lead to withdrawal if post-enrollment evaluation reveals that a participant does not meet inclusion criteria or meets exclusion criteria. Protocol non-adherence, such as a failure to follow study procedures, repeated absences from scheduled visits, or non-compliance affecting data integrity, may result in removal from the study. Pregnancy during the study requires immediate withdrawal for safety reasons. The principal investigator also retains the discretion to withdraw any participant if their continued participation is deemed unsafe or not in their best interest.

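### Section 2.10 accepts LOCF as an alternative to multiple imputation, chosen once the missing data are known, which can bias the comparison in either direction; the withdrawal rules in 2.11 can add avoidable gaps

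*Protocol article*

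**What the plan says.** Section 2.10 promises an intention-to-treat (ITT) analysis, "including all randomized patients in the analysis according to their assigned groups". It then names the methods for filling gaps: "multiple imputation or last observation carried forward (LOCF), depending on the nature and extent of the missing data". No primary method is fixed and no assumption about the missingness is given. Sensitivity analyses are promised in general terms, none of them specifically for missing data. A per-protocol analysis of patients who completed without major deviations is secondary.

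Section 2.11 lists grounds for withdrawal. Two matter here. On eligibility: "Eligibility non-compliance may lead to withdrawal if post-enrollment evaluation reveals that a participant does not meet inclusion criteria or meets exclusion criteria". On adherence: "repeated absences from scheduled visits, or non-compliance affecting data integrity, may result in removal from the study". The section does not say whether such patients continue to attend outcome visits.

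Section 2.10 also sets 127 patients per group, allowing for 30% dropout. Section 2.7 and Table 1 schedule assessments at V1 to V5, the last of them 6 months after the intervention.

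**The concern.** LOCF replaces a missing later value with the last one seen. That is right only if the marker would have stayed where it was. Sections 1 and 2.3 describe anemia, oxidative stress and immune suppression as common effects of chemotherapy, so a trend over time in both arms is plausible. If there is a shared trend and the arms lose patients at different rates, LOCF turns the dropout gap into an apparent treatment difference. If the arms lose patients equally, it shrinks a real effect. It also counts each carried-forward value as a measurement, so the reported precision is too high.

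LOCF is more than a remote option here. Repeated-measures ANOVA and the Friedman test, both named in 2.10, need every visit for a patient in their standard form. A single missed visit means either dropping the patient, against the ITT promise, or filling the value. As written, the article would allow an analysis plan to adopt LOCF as its primary method.

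Section 2.11 bears on the number of gaps. Non-adherence and late-found ineligibility are acted on after randomization. If removal from the study also ends outcome collection, ITT must rely on imputed values for patients who might have been measured.

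**Working it through.** **Inputs from the article:** 127 per group, 30% dropout, two-sided 5% level, 1:1 allocation (Sections 2.5 and 2.10). The 127 is taken as given. It cannot be rebuilt from the stated inputs, because neither the effect size d nor the SD is stated.

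**Assumptions, none from the article:** all dropouts leave before V2, so baseline is carried forward; dropout within an arm is unrelated to the marker; the marker has SD 1 at each visit; a shared change δ of 0.5 to 1.0 SD; dropout of 40% versus 20%.

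**Scale.** 0.30 × 127 = 38.1, so about 38 patients per arm have values to fill and 127 − 38 = 89 are observed.

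**Expected LOCF difference.** Let p_A and p_P be the dropout proportions on active and placebo, δ the shared change and τ the true effect. Baseline means are equal by randomization, and dropouts contribute no change:

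E(difference) = (1 − p_A)(δ + τ) − (1 − p_P)δ = τ(1 − p_A) + δ(p_P − p_A)

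| τ | δ | p_A, p_P | Result (SD) |
|---|---|---|---|
| 0 | any | 0.30, 0.30 | 0 |
| 0 | −0.5 | 0.40, 0.20 | +0.10 |
| 0 | −1.0 | 0.40, 0.20 | +0.20 |
| 0 | −0.5 | 0.20, 0.40 | −0.10 |
| 0 | −1.0 | 0.20, 0.40 | −0.20 |
| 0.40 | any | 0.30, 0.30 | 0.40 × 0.70 = 0.28 |

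Simulation agreed to within 0.005 SD. For a marker that rises (δ positive), the signs in the rows with unequal dropout reverse.

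**Rejection rate under no effect.** The shift of the test statistic is k = bias × √(127/2) = bias × 7.97, and the two-sided rejection rate is Φ(k − 1.96) + Φ(−k − 1.96).
- Bias 0.10: k = 0.80, rate about 12.5%.
- Bias 0.20: k = 1.59, rate about 36%.

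This takes the SD of the analysed values as 1. Mixing baseline and later values widens the spread: the variance in an arm becomes 1 + p(1 − p)δ². At δ = −1 that is 1.24 and 1.16, average 1.20, SD 1.095, and the upper rate falls to about 31%. The lower rate stays near 12%.

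**Smaller gap.** A 10-point gap gives a bias of 0.05 to 0.10 SD and a rate of about 7% to 12.5%.

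**Later dropout.** Suppose only half of the dropouts leave before V3, and half of those leave after V2 with half the change already seen. The gap at V3 is 0.10 and the mean unseen change is 0.75δ, so the bias is 0.10 × 0.75 × (0.5 to 1.0) = about 0.04 to 0.08 SD. By the same formula the rate is about 6% to 9%.

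**Uncertainty.** For a difference of two means with SD 1, the standard error on 127 values per arm is √(2/127) = 0.125; on the 89 observed it is √(2/89) = 0.150. LOCF reports roughly the first. A valid method would recover part of the gap from baseline and earlier visits, but not simply by counting filled values as data.

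**The case against.** - **LOCF is not the chosen method.** It is one of two examples, and multiple imputation comes first. Choosing the model is ordinary analysis-plan work, and that plan is not shown. This stands as far as it goes. But the article itself names LOCF as appropriate, and that is the statement to correct.
- **Blinding protects the choice.** Section 2.5 keeps the blind until the analysis is complete. That limits choosing a method by its result; it does not make LOCF valid. The promised sensitivity analyses do not cure this either, since none is named for missing data, and a per-protocol set of completers cannot test the missing-data assumption.
- **The direction is unknown.** This stands. A reader might infer that LOCF favours the arm that loses more patients. That holds only for a marker that falls and where higher is better. The sample-size endpoint is EPO, and Section 4 says hypoxia activates its transcription, so it could rise as anemia develops. The article gives no trend for any marker.
- **The illustration is near a worst case.** This stands. The 20-point gap has no source, and the 30% covers the whole study period. Nor does the article establish that adherence will differ by arm: session length is the same, and Section 2.6 says chamber pressure is identical while 2.6.1 and 2.6.2 give about 1500 and 1000 hPa. Those passages must be reconciled before either is relied on.
- **Section 2.11 does not contradict ITT.** This stands. A reader might infer that removed patients leave the ITT set or that their outcome collection stops. The text says neither: removal is from the study, and 2.10 still analyses everyone randomized. A condensed article may leave follow-up after withdrawal to the full protocol, and patients who repeatedly miss visits are already not providing data.

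**Conclusion.** The point holds in a limited form. The article accepts a method that can bias the comparison in either direction and that overstates precision, and it ties the choice to the missingness that occurs, in a trial expecting about 38 dropouts per arm. With no true effect, equal dropout and equal trends, the bias is nil; with a real effect and equal 30% dropout at baseline carried forward, the estimate shrinks by 30%. Under the assumed shared change of 0.5 to 1.0 SD and 40% versus 20% dropout, the spurious difference is 0.10 to 0.20 SD, with rejection of about 12% to 36% instead of 5% (about 31% at the top once the wider spread is counted). Smaller gaps and later dropout give less. These sizes are illustrations, not predictions.

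The article does not show that LOCF will be used, that bias will occur, or that ITT is broken. On 2.11, the supportable point is that removal for non-adherence or late-found ineligibility can add missing outcomes that might have been avoided. The correction should be made, since it is cheap and first enrolment is scheduled for March 2026.

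**What to change.** In Section 2.10, delete LOCF and state one primary method in advance: either a likelihood-based mixed model, or multiple imputation carried out by arm, under missing at random. Use baseline, the stratification factors (CRC stage and baseline hemoglobin) and all visits. Name at least one sensitivity analysis for data not missing at random. Section 2.10 currently gives the Mann–Whitney U test for between-group comparisons, so the text should say how that test and the chosen method fit together.

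In Section 2.11, state that patients removed for non-adherence or late-found ineligibility stay in the ITT set and are invited to the scheduled V2 to V5 visits unless they withdraw consent. Leave the medical, pregnancy and investigator-discretion grounds as they are.

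The cost is a change of wording, slightly more analysis work, and some extra follow-up at visits already planned. The number of patients that involves cannot be taken from the article, which does not split the 30% dropout by reason.
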